## Abstract

**Background:**

Chronic insomnia affects up to 63% of family dementia caregivers. Research suggests that chronic insomnia prompts changes in central stress processing that have downstream negative effects on health and mood, as well as on cognitive, inflammatory, and neurodegenerative functioning. We hypothesize that cognitive behavioral therapy for insomnia (CBT-I) will reverse those downstream effects by improving insomnia and restoring healthy central stress processing. Rural caregivers are particularly vulnerable, but they have limited access to CBT-I; therefore, we developed an accessible digital version using community input (NiteCAPP CARES).

**Objective:**

This trial will evaluate the acceptability, feasibility, and short-term and long-term effects of NiteCAPP CARES on the sleep and stress mechanisms underlying poor caregiver health and functioning.

**Methods:**

Dyads (n=100) consisting of caregivers with chronic insomnia and their coresiding persons with dementia will be recruited from Columbia and surrounding areas in Missouri, United States. Participant dyads will be randomized to 4 weeks (plus 4 bimonthly booster sessions) of NiteCAPP CARES or a web-based sleep hygiene control (NiteCAPP SHARES). Participants will be assessed at baseline, after treatment, and 6- and 12-month follow-ups. The following assessments will be completed by caregivers: 1 week of actigraphy and daily diaries measuring sleep, Insomnia Severity Index, arousal (heart rate variability), inflammation (blood-derived biomarkers: interleukin-6 and C-reactive protein), neurodegeneration (blood-derived biomarkers: plasma amyloid beta [Aβ40 and Aβ42], total tau, and phosphorylated tau [p-tau181 and p-tau217]), cognition (Joggle battery, NIH Toolbox for Assessment of Neurological and Behavioral Function, and Cognitive Failures Questionnaire), stress and burden, health, and mood (depression and anxiety). Persons with dementia will complete 1 week of actigraphy at each time point.

**Results:**

Recruitment procedures started in February 2022. All data are expected to be collected by 2026. Full trial results are planned to be published by 2027. Secondary analyses of baseline data will be subsequently published.

**Conclusions:**

This randomized controlled trial tests NiteCAPP CARES, a web-based CBT-I for rural caregivers. The knowledge obtained will address not only what outcomes improve but also how and why they improve and for how long, which will help us to modify NiteCAPP CARES to optimize treatment potency and support future pragmatic testing and dissemination.

**Trial Registration:**

ClinicalTrials.gov NCT04896775; https://clinicaltrials.gov/ct2/show/NCT04896775

**International Registered Report Identifier (IRRID):**

PRR1-10.2196/37874

## Introduction

### Background

Approximately 16 million Americans serve as unpaid informal caregivers (CGs), providing 18.6 billion hours of care, which translates into US $244 billion in health care savings [1]. The number of persons with dementia in the United States is projected to rise from 5.7 million to >14 million in the next 30 years, and most persons with dementia (70%) are cared for at home by a family member [1]. This rise in the number of persons with dementia is likely to increase the number of CGs, especially in rural areas, where populations are aging faster than those in urban areas [2]. Chronic insomnia (≥3 months difficulty initiating and maintaining sleep, early morning awakening, or nonrestorative sleep) affects up to 63% of CGs [3,4] and tends to endure (18 years on average in our CG studies) [4,5]. Factors associated with CG insomnia include changes in central stress processing (increased sympathetic nervous system arousal) [3,6] as well as worse health and daytime functioning (increased depression, stress, and cognitive dysfunction). Research [3-5] shows that cognitive behavioral therapy for insomnia (CBT-I) is an efficacious treatment for the chronic and particularly long-lasting insomnia experienced by CGs and suggests that it may restore healthy central stress processing [7]. However, rural CGs have less access to care, including CBT-I, because of significant shortages of both primary and specialty care providers in rural areas [8]. Web-based CBT-I will allow for greater dissemination, particularly for rural CGs and persons with dementia who may have challenges receiving treatment because of trained provider scarcity [9] and the burden associated with traditional in-office delivery.

It has been shown by our team as well as another group of researchers that in-person brief CBT-I (bCBT-I) improves CG sleep and mood (small to large effects) [10-12]. Early research by McCurry et al [12] found that in-person bCBT-I improved CG sleep (efficiency and quality) and depression immediately and 3 months after treatment compared with a waitlist. Our team also found that in-person bCBT-I improved sleep, depression, and anxiety in older adult CGs of persons with dementia [10]. McCrae et al [11] also found that bCBT-I (2 in-person sessions and 2 telehealth sessions) improved sleep in rural older adults for at least 3 months compared with the sleep hygiene control. Our new pilot data also suggest that CBT-I translates well to telehealth [7,13]. However, telehealth delivery still requires considerable time commitment from trained therapists (already in short supply). Thus, web delivery represents an important, logical next step that would maximize therapist time (ie, web-based moderation and feedback vs 1 hour per week one-on-one sessions), reduce CG travel burden, and give both therapist and CG scheduling flexibility. Web delivery would also enhance disseminability because the majority of Americans (including rural and older Americans) use the internet and have access to it [14]. Moreover, several meta-analyses of web-based CBT-I have indicated moderate to large effect sizes for sleep improvement that are comparable to in-person CBT-I effects [15,16]. Although web-based CBT-I has not been tested in CGs, web interventions have successfully improved noninsomnia health outcomes in stroke and CGs [7,17]. These findings provide support for the development and evaluation of web-based CBT-I for CGs (NiteCAPP CARES) in the proposed study.

Several considerations were taken into account in the development of NiteCAPP CARES. For instance, given prior work showing that providing CGs with behavioral sleep instructions for their persons with dementia led to improved sleep in persons with dementia (measured using actigraphy) [7], NiteCAPP CARES uses a dyadic approach that targets sleep for both the CG and care recipient. In addition, following recommendations from other CBT-I studies [16], NiteCAPP CARES uses a guided therapy approach with trained therapy moderators monitoring the progress of CGs and persons with dementia, providing feedback, and answering questions. Taking a dyadic, guided therapy approach may optimize the impact of CBT-I on CG mechanisms and outcomes.

Research suggests that CG chronic insomnia results in changes in central stress processing that have downstream negative effects on health and daytime functioning. CGs experience increased subjective stress and arousal because they witness the distress experienced by persons with dementia and because of the physical and time demands of caregiving [4,5]. Research shows that persons with chronic insomnia have alterations in heart rate (HR) and HR variability (HRV) while awake before sleep and during stage 2 non–rapid eye movement sleep [18], as well as lower wake-to-sleep HR reduction and SD of normal-to-normal heartbeat intervals compared with controls [19], consistent with disrupted autonomic nervous system (ANS) functioning (increased sympathetic activity). In CGs, increased self-reported stress is associated with altered HRV during the first half of sleep (lower high-frequency power values), indicative of impaired ANS functioning [19]. Our preliminary results have shown that HRV can be altered because bCBT-I increased resting HRV in adults with comorbid insomnia [10]. Collectively, the findings in comorbid insomnia and our preliminary data suggest that physiological arousal serves as a mechanism underlying other CG symptoms.

CGs also face mental and physical health–related challenges regarding mood and cognition, as well as neurodegenerative and inflammatory biomarkers. Sleep may play a role in CGs’ high levels of anxiety and depression [20] because our research shows that nights of poor sleep (ie, higher total wake time and poorer sleep quality) were associated with greater next-day negative affect in CGs [10]. Research, including ours, shows that CBT-I can improve depression in CGs [12,21,22]. In addition, CGs perform worse on tests of processing speed [23,24], attention [23,25,26], executive function [26], and memory [26,27] than same age non-CGs. Our recent trial shows that telehealth CBT-I can improve CG executive functioning and processing speed [10]. Moreover, preclinical studies link poor sleep to increased Alzheimer disease–related biomarkers (plasma amyloid beta [Aβ] and tau), suggesting that sleep is essential for protein clearance and reduction of neuronal aggregations contributing to plaques and tangles (hallmark pathology of Alzheimer disease) [27]. Risk of developing Alzheimer disease is elevated in CGs versus non-CGs (up to 6 times greater) [28], and CGs have increased peripheral inflammatory biomarker levels (eg, C-reactive protein) [29]. Sleep quality improvements are associated with reductions in inflammatory markers associated with Alzheimer disease, that is, C-reactive protein (small effects) and interleukin-6 concentrations (large effects) [29], as well as expression of inflammatory-related genes [30]. These studies suggest that targeting poor sleep may lower Alzheimer disease–related biomarker levels, thereby mitigating risk and delaying disease progression. The proposed trial will examine whether treating CGs’ sleep disturbances through NiteCAPP CARES may help mitigate their neurodegenerative risks.

The Cognitive Activation Theory of Stress [31] underlies the basic premise guiding the proposed trial, namely that CGs experience chronic insomnia, arousal, and inflammation that are associated with central nervous system changes that negatively affect other CG health outcomes (Figure 1). Specifically, arousal, poor sleep, and inflammation lead to critical changes in the hypothalamic-pituitary-adrenal axis and ANS, primarily sympathetic activation functioning, that contribute to lower health-related quality of life, increased depression and burden, and decreased cognitive functioning. We propose that NiteCAPP CARES holds promise for improving multiple CG health outcomes by improving common underlying mechanisms (sleep and arousal), thereby restoring healthy hypothalamic-pituitary-adrenal axis and ANS functioning. NiteCAPP CARES will engage these mechanisms using established sleep techniques (sleep education, sleep hygiene, and stimulus control), modified techniques (for older adults and CGs; sleep compression and brief relaxation), techniques for other CG issues (problem solving and stress management), and by targeting sleep change in persons with dementia (direct participation of persons with dementia or CG administration of behavioral techniques).

**Figure 1 figure1:**
[figure not shown]
Conceptual model. Aim 1 (not shown) examines feasibility and acceptability of NiteCAPP CARES and NiteCAPP SHARES. Sleep change in person with dementia will be examined as an outcome (aim 4) and a potential moderator (exploratory aim: dashed lines) of the relationship between changes in caregiver (CG) primary and secondary outcomes. Refer to the Outcomes section for a list of potential mediators (eg, adherence) and moderators (eg, sleep change in person with dementia, interpersonal processes, and shared lifestyle factors). Biomarkers of neurodegeneration and inflammation will be examined as exploratory CG secondary outcomes (dotted box outline). NiteCAPP CARES: cognitive behavioral therapy for insomnia; NiteCAPP SHARES: active web-based sleep hygiene and related education control.

The base NiteCAPP platform was developed in 2019 by the study team and was based on a 4-session CBT-I treatment protocol developed by the first author ([name]) and used for research [10,32] and clinical service delivery for >20 years. Initial adaptations for CGs to create NiteCAPP CARES were made following the Medical Research Council recommendations for evaluating complex medical interventions, including community participation, usability testing, and validation. The details of the preliminary work are available elsewhere [7]. Although the findings from these usability studies were promising and demonstrated the preliminary feasibility and acceptability of NiteCAPP CARES as well as its efficacy for improving sleep and other variables for CGs, they warrant further investigation in a larger sample and comparison with an active control condition across a wider range of outcomes. The proposed trial offers the following methodological improvements: inclusion of an active control group (web-based sleep hygiene and related education [NiteCAPP SHARES]), increased number and length of follow-ups, and a dyadic approach (because persons with dementia experience poor sleep and nighttime behavior that negatively affects CGs). In sum, the proposed trial addresses significant gaps in the literature and the need for effective insomnia treatment for CGs and persons with dementia.

### Objectives

The overarching goal of this randomized controlled trial (RCT) is to evaluate the acceptability, feasibility, and short-term and long-term effects of NiteCAPP CARES on the sleep and stress mechanisms underlying poor CG health and functioning. Our first specific aim is to examine the feasibility and acceptability of NiteCAPP CARES and an active web control (sleep hygiene and related education [NiteCAPP SHARES]). We hypothesize that NiteCAPP CARES and NiteCAPP SHARES will have high rates of completion (≥75% of sessions), adherence (≥75% of the techniques implemented), satisfaction (≥7.5 out of 10 on the Satisfaction Survey), and utility (≥3.5 out of 5 on the Internet Intervention Utility Questionnaire).

Our second specific aim is to examine the effects of NiteCAPP CARES on the primary (mechanistic) CG outcomes in our theory-driven conceptual model; that is, to examine the effects of 4 weeks of CBT-I compared with 4 weeks of NiteCAPP SHARES on CG sleep (insomnia severity and self-reported sleep onset latency, wake time after sleep onset, and sleep efficiency) and arousal immediately after treatment and at 6- and 12-month follow-ups. We hypothesize that compared with NiteCAPP SHARES, NiteCAPP CARES will improve CG sleep and decrease arousal.

Our third specific aim is to examine the effects of NiteCAPP CARES on the secondary CG outcomes in our theory-driven conceptual model; that is, to examine the effects of 4 weeks of CBT-I compared with weeks of NiteCAPP SHARES on CG health, mood, burden, cognition, inflammation, and neurodegeneration immediately after treatment and at 6- and 12-month follow-ups. We hypothesize that compared with NiteCAPP SHARES, NiteCAPP CARES will improve these CG outcomes.

Our fourth specific aim is to test the effect of NiteCAPP CARES on persons with dementia, the secondary outcome in our theory-driven conceptual model; that is, to examine the effects of 4 weeks of CBT-I compared with 4 weeks of NiteCAPP SHARES on sleep change in persons with dementia (objective measurement through actigraphy and total sleep time) immediately after treatment and at 6- and 12-month follow-ups. We hypothesize that compared with NiteCAPP SHARES, NiteCAPP CARES will improve sleep in persons with dementia.

Our exploratory aim is to examine the relationships between CG primary and secondary outcome changes and their potential mediators (eg, adherence) and moderators (eg, sleep change in persons with dementia, interpersonal processes, and shared lifestyle factors).

## Methods

### Trial Design and Study Setting

Dyads (n=100) consisting of CGs with chronic insomnia and their coresiding persons with dementia will be recruited from Columbia and surrounding areas in Missouri, United States, and randomized to 4 sessions of NiteCAPP CARES or NiteCAPP SHARES. The groups will receive bimonthly boosters. Baseline and posttreatment assessments as well as 6-month and 12-month follow-ups will measure sleep, arousal, biomarkers of inflammation and neurodegeneration, health, mood, burden, and cognition.

Graduate therapists and assessors will obtain written informed consent from CGs and persons with dementia, if possible. If the person with dementia is unable to consent (determined by consultation with the first author [[name]]), a legally authorized representative must sign a consent form on their behalf. If the person with dementia becomes unable to provide consent during the course of the study, the legally authorized representative will be asked to reconsent on behalf of the care recipient. Dyads in both groups will receive US $125 at baseline, US $150 after treatment, US $175 at 6-month follow-up, and US $200 at 12-month follow-up, as well as treatment at no cost. NiteCAPP SHARES participants will be offered NiteCAPP CARES at no cost after the study.

### Eligibility Criteria

The CG inclusion criteria are as follows: (1) aged ≥18 years, (2) CG living with persons with dementia, (3) willing to be randomized, (4) able to read and understand English, (5) diagnosed with insomnia [33-35], and (6) no newly prescribed or over-the-counter sleep medications for ≥1 month or stabilized for ≥6 months. Insomnia diagnosis requires (1) sleep complaints for ≥6 months, (2) adequate opportunity and circumstances for sleep, (3) at least one of the following: difficulty falling asleep or staying asleep or waking too early, (4) daytime dysfunction (mood, cognitive, social, or occupational) because of insomnia, and (5) baseline diaries indicate >30 minutes of sleep onset latency or wake after sleep onset on ≥3 nights.

The CG exclusion criteria are as follows: (1) unable to consent, (2) cognitive impairment (based on score of ≤25 on the Montreal Cognitive Assessment), (3) sleep disorder other than insomnia (ie, apnea (Apnea-Hypopnea Index score>15), (4) bipolar or seizure disorder, (5) other major psychopathology except depression or anxiety (eg, suicidal or psychotic), (6) severe untreated psychiatric comorbidity, (7) psychotropic or other medications (eg, clonidine) that alter sleep, and (8) nonpharmacological treatment for sleep or mood outside of current trial.

The inclusion criteria for persons with dementia are as follows: (1) probable or possible Alzheimer disease (self-report or primary care physician’s written confirmation), (2) at least one problem on the Nighttime Behavior Inventory ≥3 nights per week, (3) able to tolerate actigraphy, (4) not taking any new sleep medications for ≥1 month or stabilized ≥6 months, (5) untreated sleep disorder for which CBT-I is not recommended (ie, sleep apnea), and (6) scoring <32 on the sleep apnea scale on the Sleep Disorders Questionnaire.

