### Randomization and Blinding

Computer randomization will be performed by the team’s biostatistician, using a permuted block randomization technique stratified by baseline sleep medication use (yes or no) [36]. Other personnel (except for therapists, supervisor, and project coordinator) will be blinded to randomization.

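### Item 5 of the inclusion criteria for persons with dementia is an exclusion-type condition printed as an entry requirement; it opposes item 6 and must be reconciled with it

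*Protocol article*

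**What the plan says.** All the text at issue is in the protocol article, under Eligibility Criteria and under Randomization and Blinding.

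**Persons with dementia.** There is one list, and it opens as an inclusion list: "The inclusion criteria for persons with dementia are as follows: (1) probable or possible Alzheimer disease". Its last two items are "5) untreated sleep disorder for which CBT-I is not recommended (ie, sleep apnea), and (6) scoring <32 on the sleep apnea scale". No exclusion list for persons with dementia follows.

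**Caregivers, apnea.** Here the condition is in the exclusion list: "3) sleep disorder other than insomnia (ie, apnea (Apnea-Hypopnea Index score>15".

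**Caregivers, medication.** Inclusion criterion: "6) no newly prescribed or over-the-counter sleep medications for ≥1 month or stabilized for ≥6 months". Exclusion criterion: "7) psychotropic or other medications (eg, clonidine) that alter sleep".

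**Randomization.** Allocation is made "using a permuted block randomization technique stratified by baseline sleep medication use (yes or no". The sentence does not say whether the factor refers to the caregiver, the person with dementia or either of them.

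**The concern.** An inclusion list states what must be true for a person to enter. Item 5 describes a disorder that the article itself says the tested therapy does not suit, yet its place in the list makes that disorder a condition of entry.

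This matters more here than in a trial where the person with dementia is only observed. In NiteCAPP CARES, session 2 sets a sleep prescription for both members of the dyad, and sessions 3 and 4 update it. The home apnea test in screening stage 3 is described for caregivers only. In the article, items 5 and 6 are therefore the only stated criteria on apnea for persons with dementia, and the two point in opposite directions. These people's actigraphy is also the Aim 4 outcome, so the population for that aim is not clearly defined.

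The medication wording raises a smaller question. Stratifying by sleep medication use presupposes that some users are enrolled. Read broadly, a caregiver exclusion for drugs that alter sleep could remove users whom the caregiver inclusion list admits.

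**Working it through.** No arithmetic applies. The check sets the criteria against each other.

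**Step 1. Can item 5 be read as a negative?** The heading is positive (inclusion), and item 5 contains no negating word of its own. Item 4 of the same list carries its own negation, about new sleep medication, so negation in this list is written item by item. Item 5 therefore cannot take one from the heading.

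**Step 2. Who is eligible under each reading of item 5, with item 6 applied?**

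| Untreated disorder | Apnea-scale score | Item 5 as printed (required) | Item 5 as a bar |
|---|---|---|---|
| present | below 32 | eligible | not eligible |
| absent | below 32 | not eligible | eligible |
| present | 32 or more | not eligible | not eligible |
| absent | 32 or more | not eligible | not eligible |

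The two readings have no eligible row in common. The printed combination is not a logical impossibility, because the first row can occur: a questionnaire score below 32 does not prove that apnea is absent. Items 5 and 6 are opposed in purpose but not strictly incompatible.

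**Step 3. Does other text settle the direction?** Item 6 screens against apnea, and caregiver exclusion 3 does the same for the other dyad member. Both run against the printed sense of item 5. Nothing in the article supports requiring the disorder.

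**Step 4. Caregiver medication.** Exclusion 7 can be read broadly (any drug that alters sleep, sleep medication included) or narrowly (drugs other than the sleep medication already governed by inclusion 6). The stratification factor can refer to the caregiver, the person with dementia or either member. Item 4 for persons with dementia admits stabilized sleep medication, and exclusion 7 applies to caregivers only. The table shows whether the stratum of users can be filled.

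| Factor refers to | Exclusion 7 broad | Exclusion 7 narrow |
|---|---|---|
| caregiver | no | yes |
| person with dementia | yes | yes |
| either member | yes | yes |

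That gives 3 × 2 = 6 combinations. The stratum is empty in one of them, which needs both the broad reading and a caregiver-only factor. The article states neither.

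**The case against.** The strongest reply is that item 5 is a visible drafting slip, either a lost negation or an exclusion placed in the wrong list. On this view no sensible screener would apply it as printed, since the item itself says the therapy is unsuitable and item 6 screens the other way. The Ethics Approval section also refers to a study protocol and a manual of operating procedures that were reviewed separately and are not shown; they may be worded correctly.

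Much of this stands. A slip is the likeliest explanation, and the article gives no evidence that anyone was wrongly enrolled or turned away. But the likely cause does not correct the text. This is a stated eligibility rule with the wrong sense, not a detail that an article leaves to a fuller document.

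A reader might go further and infer that the trial would enrol almost nobody, or that the Aim 4 effect would be diluted. The article does not support either. It gives no figure for how many persons with dementia have an untreated disorder and score below 32, and nothing on how such a disorder would change the treatment effect. Items 5 and 6 can also both be met.

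On medication, the reply is stronger. Inclusion 6 is a specific rule for sleep medication with its own stability condition, while exclusion 7 is general and gives clonidine as its example. Letting the specific rule govern sleep medication leaves inclusion 6, exclusion 7 and the stratification factor each with a purpose. That is a reasonable reading, but the article does not state it, so a request for clarification remains.

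**Conclusion.** The point on item 5 holds. The eligibility text for persons with dementia is wrong as printed: it requires a condition for which the article says the tested therapy is not advised, it opposes item 6, and no exclusion list offsets it. The rule bears on every person with dementia screened, and reversing its sense reverses eligibility for everyone who passes item 6. This conclusion rests on the wording alone and on no assumption about prevalence or effect size. It does not establish that actual screening followed the printed wording.

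The medication point is secondary and less certain. Inclusion 6, exclusion 7 and the stratification factor are not reconciled in the text, and the dyad member who defines the stratum is not named. A reader might conclude that the stratum of users is empty. That needs two readings that the article does not state, so it is not established.

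**What to change.** - **Items 5 and 6 for persons with dementia.** The sponsor should reconcile them so that they point in the same direction, and make the article, the full protocol and the manual of operating procedures agree. Which eligibility rule applies is for the sponsor to decide and state.
- **Screening records.** Recruitment procedures began in February 2022 (Results section). Check that persons with dementia screened since then were handled according to the reconciled text, and report any who were not.
- **Caregiver medication.** Reconcile inclusion 6, exclusion 7 and the stratification factor by stating whether exclusion 7 covers stabilized sleep medication. State whether the caregiver's use, the use by the person with dementia, or use by either member defines the stratum.

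The cost is a few lines of corrected wording and a review of existing screening records. The changes requested here alter no sample size, outcome or analysis model.
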